Here, we investigate how digital phenotyping integrated with clinical (endo)phenotypes constitutes a new method for building comprehensive datasets based on digital epidemiology to create meaningful metrics of cognition, emotions, and behavior specific to children and adolescents. These detectable and measurable features will help understanding better brain development and hereby identifying prominent predictive variables to achieve dimensionality reduction and risk factors for NDDs.

**Purpose** (Table 1)—the EPIDAI4Kids study will examine brain functioning in children aged 7 to 12 years using biometrics and digital biomarkers to create meaningful metrics of cognition, emotions, and behavior specific to children and adolescents, while they are playing at gamified assessments on an unmodified tablet.

**Table 1 tab1:** Primary and secondary objectives, research questions, and hypotheses.

Primary objective	Research question	Outcome	Measures	Testable hypothesis
To create and compare a normative base of brain functioning in children aged 7 to 12 years using multimodality biometry e-measurements vs. paper-based screening	Is the neuro-developmental e-assessments as or more acceptable to children and health practitioners than paper-based screening?	Acceptability: % children in the study failing finishing the e-assessments	Acceptability	Higher proportion of children and health practitioners will affirmatively respond to acceptability for the e-measurement
		% of participants reporting that e-questions and psychometric games are easy to navigate around on the tablet	Qualitative; semi-structured interview	
			Quantitative: proportion of participants feeling uncomfortable	
To compare psychometric properties (sensitivity, specificity, cutoff points) of paper-based screening vs. the psychometric games?	What are the performances in cognition, emotion and/or behavior in children aged 7 to 12 years on child neurodevelopment?	Efficiency: correlations between scoring of paper-based screening performances and biometrics within each participant and inter-examinator	Quantitative: video and audio will be recorded for about 30 min while the children are playing on a unmodified tablet. Eye-, face- digit- and sound- will be extracted from recorded video by ML/DL algorithms.	Strong correlations between paper-based screening performances (psychometric properties) and multimodality biometrics within each participant.

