#### Sampling

We will account for variations across population and strive to identify the broad range of social and environmental influences on brain function and development. Such an approach may ultimately reveal a much more complex tapestry of etiological mechanisms than are typically derived from averaging over a relatively homogenous sample. Based on our own experience and previous sampling frame to access a representative sample of the larger heterogeneous population of children (66–69) and using three broad dimensions of phonological processing abilities, executive skills and processing speed (70) with latent factor analysis (71), we estimated that the final sample size is 400 children (half boys and half girls) for power analysis of 0.8, a confidence level of 0.05, and a type I error to detect medium to small effects over the study’s duration (72) Because we except a 20% attrition rate at each critical step: the enrollment process till the data collection completion, we have estimated that 786 participants (Figure 1) will be needed to provide a comprehensive understanding of changes through the test batteries assessing numerous factors impacting brain functioning.

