#### Hypothesis testing framework

Hypotheses will be tested at the α = 0.05 level after adjustment for multiple tests. Significant statistics only will be converted to indices of effect size and their associated confidence interval. The primary analytical framework will be nested linear mixed models with random effects (LMEs), and Cox proportional hazards models to handle quantitative predictor variables and categorical variables.

For LMEs, the primary effects of interest will generally be the interaction between independent variables and time (e.g., the visit number). Analyses will be performed with multiple levels of nesting (e.g., site, devices) that are not of intrinsic interest, as well as nesting within participants over time, allowing all data to be used for wide analyses. Age and gender will be specified as co-variables and others such as demographic and other background variables will be specified upon scientific and empirical considerations.

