## Discussion

We have described EPIDIA4Kids, a study protocol to evaluate how multimodality biometry relying on digital epidemiology can give insight into brain functioning in children aged 7 to 12 years. While they are playing psychometric games on an unmodified tablet, multi-stream data will be collected from 400 children volunteers independently of NDD diagnosis.

Multivariate linear models for brain functioning scores will be obtained by using supervised machine/deep-learning and cross-validation. Those models will include variables from the collected biometric data such as emotion estimates, eye-tracking features, digit-trajectories, correction rates and response time during game’s performances. Each brain functioning scores estimated by each biometric model will be agreed with each score of one or some questionnaires. This multimodality approach (73) reflects the recent advances in both quantity and quality of data available since Information & Communication Technology (ICT) and Internet of Things (IoT) brings high potential for improved accuracy at cost-efficiency (24, 28). Machine learning and AI applied to NDDs may open valuable route to examine heterogenous symptoms in pediatric population and at individual level, by integrating multimodality dimensions in prediction models, such as social, environmental, and structural determinants (74–76). Furthermore, the models can handle for missing data and larger numbers of interactive predictors. The so-called digital epidemiology could thus provide support more accurate and objective diagnostic and therapeutic decision making to health practitioners in their practice.

However, while we aim at building comprehensive datasets to create meaningful metrics of cognition, emotions and behaviors based digital epidemiology, we will carefully review data quality to lower response bias (e.g., youth’s illectronism, intra-and inter-examiner variance) by, for instance, minimizing heterogeneity of hardware implementation, and AI-related bias (e.g., over/underfitting). Furthermore, these *de novo* biometrics will require mix adjustment to ensure that observed differences in outcomes are relevant to the actual clinical categorization.

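### The primary efficiency hypothesis is about strong correlations, but no minimum value is set, and the only stated decision rule, adjusted significance at 0.05, is met by weak correlations at N = 400

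*Protocol article*

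**What the plan says.** Table 1 lists the efficiency outcome under the primary objective: "Efficiency: correlations between scoring of paper-based screening performances and biometrics within each participant and inter-examinator". In the column for testable hypotheses the entry is "Strong correlations between paper-based screening performances (psychometric properties) and multimodality biometrics within each participant". No value, minimum r or confidence bound is given for 'strong' anywhere in the article.

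The section Hypothesis testing framework states the decision rule: "Hypotheses will be tested at the α = 0.05 level after adjustment for multiple tests". It does not give the adjustment method, the number of tests, the sidedness or the null value. It then adds: "Significant statistics only will be converted to indices of effect size and their associated confidence interval". No threshold is attached to those effect sizes.

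The Sampling section says "we estimated that the final sample size is 400 children (half boys and half girls) for power analysis of 0.8", and describes the target as "to detect medium to small effects over the study’s duration". No numeric effect size is given.

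Table 3 assigns convergent measures to each construct, often more than one. The Discussion says of the model scores: "Each brain functioning scores estimated by each biometric model will be agreed with each score of one or some questionnaires". It also says that the models will be built with cross-validation.

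**The concern.** The hypothesis and the rule that is meant to test it concern different things. The hypothesis is about how large the correlation is. A significance test, with no null value stated, asks only whether the correlation differs from zero. At several hundred children the two answers can be far apart.

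This goes further than a word left undefined. The article states both a hypothesis and a rule, and the rule as written does not address the hypothesis. Size enters only afterwards, as description, and only for results that have already passed. Where a construct has several comparators, the deciding pair is also not fixed, so a low bar can be tried in more than one way.

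What is at stake is how convergent validity is judged for a tool that the article hopes will serve as a first-line evaluation of neurodevelopmental disorders.

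**Working it through.** **Inputs.** From the article: N = 400 (Sampling; Recruitment gives the same target), power 0.8, alpha 0.05 after adjustment (Hypothesis testing framework), and 17 rows in Table 3. Assumed because not stated: a null of zero, two-sided tests, one pair of scores per child, and Bonferroni as the adjustment.

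**The plan's own figure.** The 400 cannot be reproduced, because the effect size is given in words only. Solving backwards with n = ((1.96 + 0.84)/atanh r)² + 3, r = 0.14 needs 399 children. So 400 gives 80% power at a true correlation of about 0.14. This agrees with the article's description of the target as medium to small effects, and it is far from strong. The enrolment figure follows roughly from three steps of 20% loss: 400/0.8³ = 781, against 786 stated.

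**Smallest correlation that meets the rule.** Critical |r| = t/√(n − 2 + t²), with n − 2 = 398.

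| Tests adjusted for | t | Critical \|r\| | Variance (r²) |
|---|---|---|---|
| 1 (no adjustment) | 1.966 | 0.098 | 1.0% |
| 17 (rows of Table 3) | 2.992 | 0.148 | 2.2% |
| 1000 | 4.101 | 0.201 | 4.1% |

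The first line in full: 1.966/√(398 + 3.865) = 0.098. A one-sided unadjusted test would lower it to 0.082. Step-up procedures (Hochberg, Benjamini-Hochberg) can bring the bar back to 0.098 when all tests are significant.

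**How often a weak correlation passes.** For a true r of 0.20 (4% of variance), power = Φ(atanh(0.20) × √397 − z), with atanh(0.20) × √397 = 0.2027 × 19.92 = 4.04.
- Unadjusted: Φ(4.04 − 1.96) = 0.98.
- At 0.05/17: Φ(4.04 − 2.97) = 0.86.

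**What a test of size would need.** Let rho0 be the chosen minimum. The observed r whose lower limit equals rho0 is tanh(atanh(rho0) + z/√397). The article gives no rho0, so three assumed values are shown. The last column is the true r with 80% power under the 95% interval, tanh(atanh(rho0) + (1.96 + 0.84)/√397).

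| rho0 (assumed) | Observed r, 95% CI (z = 1.96) | Observed r, Bonferroni over 17 (z = 2.97) | True r for 80% power, 95% CI |
|---|---|---|---|
| 0.3 | 0.39 | 0.43 | 0.42 |
| 0.5 | 0.57 | 0.60 | 0.60 |
| 0.7 | 0.75 | 0.77 | 0.76 |

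For rho0 = 0.5 and the 95% interval: tanh(0.549 + 1.96/19.92) = tanh(0.648) = 0.57. Under each of these readings of 'strong', the stated rule passes correlations well below the claim.

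**The case against.** The best case against the point is that a cut-off for 'strong' and the null for each test are details that a journal article commonly leaves to the full protocol or the analysis plan, neither of which is shown. The section on testing names mixed models and Cox models and describes no correlation test, so the test against zero is supplied by the reader. On plain reading, r = 0.10 fails a hypothesis that says strong, and a weak significant result would show as weak in its reported interval.

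Part of this stands. The zero null, the single pair per child and Bonferroni are assumptions and are marked as such. The table's wording about correlation within each participant is unclear, whereas one pair per child gives a between-child correlation. If the omission of a number were all, it would not be a finding. What remains is that the rule the article does state does not match the hypothesis it does state, and that the named models add no size criterion.

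Three stronger readings are tempting, and the article does not support them.
- **A negligible correlation would confirm the tool.** The article never equates significance with validation. Its primary objective also covers sensitivity, specificity, reliability, reproducibility, predictive values and acceptability.
- **The bar is 0.10.** That ignores the promised adjustment. It is the two-sided, unadjusted floor; about 0.15 is the fairer figure under Bonferroni over Table 3.
- **The comparators are open-ended.** Table 3 limits them to named measures. The Discussion sentence concerns model scores and is not a decision rule. The gap is only that no single deciding pair is named where several are listed.

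**Conclusion.** The point holds in a limited form. The adjusted significance rule cannot by itself test a hypothesis of strong correlation. With 400 children, a null of zero and one pair of scores per child, it is met at |r| of about 0.10 to 0.20 (1% to 4% of variance), depending on an adjustment that the article does not specify. Even an extreme correction leaves the bar at about 0.20.

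How far this falls short depends on what 'strong' means, which the article does not say. The values 0.3, 0.5 and 0.7 are illustrations only. The conclusion concerns the fit between rule and hypothesis; it does not predict what the study will claim. It should be corrected before analysis, as the correction needs no new data.

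**What to change.** 1. State the minimum correlation before analysis. The sponsor should choose the value and justify it for the intended use.
2. Call a construct supported only if the lower limit of its multiplicity-adjusted confidence interval, computed on the cross-validated biometric scores, exceeds that value. Name the adjustment method and the number of tests.
3. Name one deciding comparator per construct from those in Table 3, and treat other pairings as exploratory.
4. Report r and its interval for every construct, not only for the significant ones.
5. Say whether the correlation is between children or within a child.

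The cost is wording and one agreed threshold, using data already planned. The sample is workable: with a bound of 0.5 and an unadjusted 95% interval, 400 children give 80% power at a true r of about 0.60. The downside is that fewer constructs will be declared supported, and multiplicity adjustment raises the required r a little further (0.57 to 0.60 for that bound over 17 tests). Passing this test would support convergent validity only. Showing that the e-measure can replace the paper score would need an analysis of agreement.

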There is a clear need for a rigorous evaluation of the feasibility, acceptability, and psychometric performance of e-screening for large scale children and adolescent cohort. A key consideration for evaluation is to determine whether gamified e-screening delivered through an unmodified tablet are valid and reliable for use compared to well-established assessment tools. For example, it has been shown that some tools have different psychometric properties when delivered online, suggesting a need for different cutoff points (35).

Taken together, the need to identify screening and assessment tools that are acceptable to both children and health professionals, overcome barriers to accessibility-to-care, to implementation into routine care, and are cost-effective and clinically useful, is crucially needed.

Today, billions of people are increasingly generating and collecting health-related data online (36) or on mobile devices. The opportunities for more accurate and effective health services are enormous (37, 38). Digital epidemiology uses the new and rapidly expanding digital data streams from mobile devices to advance public and personalized health (39, 40). These datasets are then used by artificial intelligence algorithms to improve our understanding of health and disorders dynamics, both in individuals and in the general population. In natural environment, digital epidemiology represents a new approach that aims at measuring human behavior and may, combined with clinical (endo)phenotypes, enhance capability and sensitivity in early identification, diagnosis, and management of health conditions. Moreover, such a combined approach may easily allow clinicians to perform a more personalized and patient-tailored diagnostic and therapeutic approach.

As children and adolescents are so familiar with digital technologies (41, 42), building the right services specifically designed and dedicated to them will help to prevent, monitor, and intervene more appropriately on neurodevelopmental and related mental disorders at a larger scale.

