### Primary objective

The primary objective of the study is to determine whether a normative base relying on multimodality biometry e-measurements tool, called XAI4Kids®, can evaluate brain functioning, i.e., the psychometric properties (sensitivity, specificity, reliability, reproducibility, and positive/negative predictive values) in children aged 7 to 12 years and evaluate the efficiency and acceptability of such e-screening tool compared to various current convergent validity measures of brain functioning (Figure 2).

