**Figure 2 fig2:**
[figure not shown]
The EPIDIA4kIDS proposed framework. We will collect data from varied sources, including participant information with questionnaires and semi-structured interviews regarding their background, demographics, and medical history. Using unmodified tablet, we will gather data from video, digit-tracking, and EEG (for a sub cohort) as time-series logs. Based on various performance metrics, relevant features will be extracted automatically using various machine and deep learning algorithms to create a store of features clinically relevant based on the literature. Relevant features will be then processed and selected through statistical analysis and model selection that combined model training and model serving. Afterwards, analysis is performed to validate the relevance of the selected metrics for identification of cognitive, behavioral, and emotional states related to NDDs. EEG, Electroencephalogram; PCA, Principal Component Analysis; ADHD, Attention Deficit Hyperactivity Disorder; ASQ, Autism Spectrum Disorder; SLD, Specific Learning Disorders; DMD, Developmental Motricity Disorder; ROC, Receiver Operating Characteristic.

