▪ The first one is to merge the features from the multiple signals, and structure them as multivariate time series ready to be used by machine learning models, since the prediction approach discussed is dynamic and will consider the dynamic aspect of the data. High-level feature extraction will be validated by expertise of psychologists and physicians. This choice is mainly for the explicability of the outputs of the system since it allows to detect the most relevant features and to find the causal relationships between them the target variables and the input features. This part can include already trained AI models. For example, the use of already trained deep learning networks for the detection of face and eye points, head position, etc., … This extraction also includes domain expertise. The latter is very important in this domain, i.e., high-level feature extraction from multimodal signals, as it is used to design what to extract in such a way that it is interpretable and effective for prediction based on human experience.▪ A second step of variable selection will be applied to reduce the set of input variables and to identify the most relevant features. This step will also be useful for the output of the prediction module to detect causal relationships between high-level behavioral characteristics and the variables to be predicted, for example, children’s attention scores. On a technical level, the methods applied in this stage are part of the “feature selection” methods and can be supervised or unsupervised machine learning methods. In the learning phase, several methods can be tested to find the best one for each attention score.▪ The third step is summarized in the prediction module which consists in applying prediction models with a sequence-to-label strategy, since the novelty of this tool will be to predict the scores of cognitive, metacognitive and behavioral functions in a dynamic way, i.e., to predict an attention score at an instant of time according to the past temporal sequences of the features extracted in the second step of the prediction module. The length of the sequences will be studied in more detail soon depending on the size of the available behavioral signals and will be adjusted in such a way as to improve the predictions. In this context, the classifiers used will be recurrent neural networks, for example the LSTM (Long Short-Term Memory) network, and transformers. A second feature can be easily added to the prediction tool which consists in classifying the children (NDD/neurotypical) starting only from the high-level features extracted from the raw behavior signals, without the need for labels (attention scores). In this case, unsupervised learning models of the “clustering” type are applied.

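### Table 1 sets out to compare sensitivity, specificity and cut-offs, but its only accuracy outcome is an unquantified strong correlation, which a score that screens poorly can meet

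*Protocol article*

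**What the plan says.** All references are to the protocol article.

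- **Table 1, second primary-objective row, objective:** "To compare psychometric properties (sensitivity, specificity, cutoff points) of paper-based screening vs. the psychometric games".
- **Same row, outcome:** "Efficiency: correlations between scoring of paper-based screening performances and biometrics within each participant and inter-examinator".
- **Same row, testable hypotheses:** "Strong correlations between paper-based screening performances (psychometric properties) and multimodality biometrics within each participant". The other hypothesis in the row concerns variability between examiners, not accuracy. No value is given for a strong correlation.
- **Primary objective section:** names sensitivity, specificity, reliability, reproducibility and positive and negative predictive values as the properties to be evaluated. It states no reference cut-off and no success criterion.
- **AI modeling, third step:** the model is "to predict the scores of cognitive, metacognitive and behavioral functions in a dynamic way", with an attention score as the example.
- **Discussion:** "Each brain functioning scores estimated by each biometric model will be agreed with each score of one or some questionnaires". No statistic is attached to the agreement.
- **Figure 2 legend:** lists "ROC, Receiver Operating Characteristic" among its abbreviations. The figure itself is not available.
- **Introduction:** notes that some tools behave differently when delivered online, "suggesting a need for different cutoff points (35"). No rule for setting such a cut-off follows.

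**The concern.** The outcome printed for the row does not measure the row's objective. Sensitivity, specificity and cut-off points describe classification at a threshold, and for a screening tool that threshold lies in the tail of the distribution. A correlation summarises linear association over the whole range. Two scores can correlate strongly while one of them misses a large share of the children whom the other calls low. Adding a constant to the e-score, or compressing its scale, leaves the correlation unchanged, although either can change who falls below a fixed cut-off.

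Because strong is not quantified, nothing excludes the range of correlations in which detection of low scorers is weak. The study could then report its primary efficiency hypothesis as met while the tool, which the article proposes as a first-instance evaluation for neurodevelopmental disorders, detects about half of the low scorers or fewer.

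**Working it through.** The article states no figure for correlation, agreement or sensitivity, so there is none to reproduce. The calculation below is an illustration.

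**Assumptions (none is in the document).** Paper score Y and e-score X are standardised and bivariate normal with correlation r. A low score is Y < c. I take r = 0.7, 0.8 and 0.9, and c = -1, -1.5 and -2 SD.

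**Step 1. Cut-off matched to flag the same share.** The e-score cut-off is set so that the share flagged equals Φ(c). Then

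sensitivity = P(X < c, Y < c) / Φ(c).

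At c = -1.5, Φ(c) = 0.0668:
- r = 0.7: 0.0282 / 0.0668 = 0.42
- r = 0.8: 0.0349 / 0.0668 = 0.52

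At c = -1, Φ(c) = 0.1587:
- r = 0.7: 0.0840 / 0.1587 = 0.53
- r = 0.8: 0.0976 / 0.1587 = 0.62

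| Paper cut-off | Share low | r = 0.7 | r = 0.8 | r = 0.9 |
|---|---|---|---|---|
| -1 SD | 15.9% | 53% | 62% | 73% |
| -1.5 SD | 6.7% | 42% | 52% | 66% |
| -2 SD | 2.3% | 32% | 43% | 59% |

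This already allows the e-score its own cut-off. The remaining loss comes from r being below 1.

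**Step 2. Constant bias.** Let the e-score have the same SD as the paper score but read 0.5 SD too high, and apply the cut-off c unchanged. Then

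sensitivity = P(X < c - 0.5, Y < c) / Φ(c).

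At c = -1 and r = 0.8: 0.0530 / 0.1587 = 0.33, against 0.62 without bias. The correlation is 0.8 in both cases. Re-deriving the cut-off on the e-score restores 0.62.

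**Step 3. Scale compression.** If X is turned into a least-squares prediction of Y, its SD is r times that of Y. Applying c unchanged flags Φ(c/r). At c = -1.5:
- r = 0.7: flags 1.6%, sensitivity 15%
- r = 0.8: flags 3.0%, sensitivity 31%

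Again r is unchanged, and a re-derived cut-off returns the values in Step 1. This is the least favourable case, and the article does not propose using the paper cut-off in this way.

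**Step 4. What each statistic would show.** The prediction in Step 3 is perfectly calibrated: regressing Y on it gives slope 1 and intercept 0, and the mean difference is 0. Calibration and mean difference would therefore not reveal the low sensitivity. Its limits of agreement are ±1.96·√(1 - r²) SD, that is ±1.40 SD at r = 0.7 and ±1.18 SD at r = 0.8, so they depend on r alone. Only sensitivity and specificity at a stated cut-off show the loss directly. The bias in Step 2 would appear in the mean difference.

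**The case against.** **Table 1 correlates biometrics, not predicted scores.** The row's measures cell describes signals extracted from video, and Table 3 pairs games and data streams with paper tests as convergent validity measures. For a raw game metric on its own scale, correlation is a suitable convergent measure. This stands. That the correlated quantity is a model-predicted paper score is something a reader might infer from AI modeling and the Discussion, but no passage says so. The mismatch between objective and outcome does not depend on that inference.

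**Sensitivity, specificity, predictive values and ROC are named elsewhere.** This also stands, and it rules out saying that the tool is judged by correlation alone. If reported, those measures would expose poor detection. They are named as objectives or abbreviations, however, without a reference cut-off or criterion, and the accuracy hypothesis stays correlational.

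**A reader might conclude that a strongly correlated score will miss most low scorers.** The documents do not support this. It requires the paper cut-off to be applied unchanged to a compressed prediction. The Introduction points towards different cut-offs, and Table 1 makes cut-offs an object of study. Even in that scenario, sensitivity exceeds 50% once r passes about 0.82 at -1 SD or 0.89 at -1.5 SD. Nor is compression guaranteed: it holds for least-squares fits, not for every held-out neural-network prediction.

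**The distribution is assumed.** The cohort requires an estimated IQ of 85 or above and mixes typically developing and diagnosed children, so an untruncated normal is only a rough guide.

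**The agreement statistic may be left to a fuller document.** That is fair for the Discussion sentence taken alone. It does not cover the Table 1 outcome, which is stated and does not fit its objective.

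**Conclusion.** The point holds as a mismatch between a stated primary objective and the outcome and hypothesis fixed for it. With the e-score cut-off matched to the paper prevalence, correlations of 0.7 to 0.8 correspond to sensitivities of 42% to 52% at -1.5 SD and 53% to 62% at -1 SD. Where the cut-off is not re-derived, a bias of 0.5 SD lowers sensitivity from 62% to 33% at -1 SD and r = 0.8, with no change in r. These sizes rest on bivariate normality and on values of r and the cut-off that the article does not give. They show what the hypothesis permits and do not predict how the tool will perform. The change should be made, but the study's data collection is not in question.

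**What to change.** 1. Keep correlation as the convergent validity measure for raw game metrics, and state what value counts as strong.
2. Make the accuracy outcome of the Table 1 row match its objective: held-out sensitivity and specificity with confidence intervals, against a stated paper reference cut-off for each measure, at an e-score cut-off derived in the training folds.
3. Where a model predicts a reference score on that score's own scale, define the agreement mentioned in the Discussion as mean difference and limits of agreement, with the calibration slope. These add to item 2 and cannot replace it.

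The cost is extra tables from data already planned. Results will look less favourable than a correlation and will be less precise, because few children fall in the tail. With 400 completers and the same normal assumption, about 400 × 0.0668 = 27 lie below -1.5 SD. A sensitivity of 52% would then carry a 95% interval of roughly ±1.96·√(0.52 × 0.48 / 27) = ±19 percentage points.
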